#### Statistical analysis

2.7.2

All the data will be analyzed in R (v. 3.4.3). Continuous variables will be presented as means and standard deviation while categorical variables as number and percent of subjects. For categorical variables, differences between patients will be analyzed using Pearson Chi-squared test. For continuous variables, the Kolmogorov–Smirnov test will be applied to check the distribution of data. In the case of normally distributed data independent *t* test will be used to compare patients, whereas Mann–Whitney *U* test will be used for non-normal distributions. Effectiveness of analyzed parameters and composite parameters in indicating the patient's fulfilling primary and secondary outcomes will be assessed using logistic regression. For all analysis, *P*-value <.05 will be considered significant.

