### Trial design

2.1

The LUCY study is an observational, cohort, prospective, 2-stage trial.

Designed in the study interactive patient's assistant, also called LUCY will be a mobile application, a database and a machine learning system operating as a data integrator. During the first stage of the study LUCY will be initiated. The relevant parameters for patient's endpoints prediction will be collected from data from remote device's interrogation via Medtronic CareLink Express (MCLE) system and health status reported by patients. Implemented real-time self-learning algorithm will predict the necessity of ambulatory visit. In the second stage of the study, the effectiveness of LUCY's prediction of patient's endpoints will be assessed.

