### Outcome assessment

2.5

The outcome of the study is a true positive result of the LUCY's estimation in predicting primary and secondary endpoint in the second stage of the trial.

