#### Sample size calculation

2.7.1

During the survey planning, we calculated the sample size required to assess the correlation between input data and primary outcome as 311, due to results of previously performed and published study (alpha = 0.01, study power = 0.95, the odds ratio for outcome indication = 3.3, outcome prevalence = 30%).^[4]^ We used G∗Power software 3.0.1.0 downloaded from http://www.gpower.hhu.de [S1]. The final number of subjects planned to input into the study is a double of calculated size (one for each stage of the trial).

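### Stage 2 is meant to show that LUCY classifies visits correctly, but the only stated analysis of effectiveness and the sample size concern association

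*Protocol article*

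**What the plan says.** All references are to the protocol article.

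- **2.1 Trial design** gives the purpose of stage 2: "In the second stage of the study, the effectiveness of LUCY's prediction of patient's endpoints will be assessed".
- **2.5 Outcome assessment** names the outcome: "The outcome of the study is a true positive result of the LUCY's estimation in predicting primary and secondary endpoint in the second stage". This is a classification result.
- **2.3 Study population** supplies the comparator. Every patient is seen by an expert cardiologist who does not know LUCY's result, and the cardiologist's decisions are set against LUCY's evaluation.
- **2.7.1 Sample size calculation** arrives at 311 for the relation between input data and the primary outcome, using "alpha = 0.01, study power = 0.95, the odds ratio for outcome indication = 3.3, outcome prevalence = 30"%. It then doubles that size so that each stage has one. Section 2.3 gives 300 per stage.
- **2.7.2 Statistical analysis** contains the only sentence on how effectiveness is analysed: "Effectiveness of analyzed parameters and composite parameters in indicating the patient's fulfilling primary and secondary outcomes will be assessed using logistic regression". It closes with a general rule: "For all analysis, *P*-value <.05 will be considered significant".

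**The concern.** The declared outcome and the declared analysis answer different questions. A true-positive result asks how many of the necessary visits LUCY picks out. A logistic coefficient tested at P<.05 asks only whether the odds ratio differs from 1. The sample size carried into stage 2 was derived for the second question as well.

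LUCY is intended to identify visits that can be skipped, so the error that matters most is a necessary visit left unflagged. If the stage-2 conclusion came to rest on a significant association, a tool that misses most necessary visits could be described as effective. The reader could not tell whether the claim concerned association or accuracy.

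**Working it through.** **Inputs from the article.** 300 patients in stage 2 (2.3); outcome prevalence 30% and odds ratio 3.3 (2.7.1); P<.05 (2.7.2).

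**Assumptions, not in the article.** LUCY's output is a yes/no flag, the test is a two-sided Wald test, and the prevalence applies to stage 2. LUCY's sensitivity, specificity and flag rate are not given, so ranges are shown.

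**Step 1. The plan's own figure.** The 311 can be neither confirmed nor refuted, because the distribution of the predictor is not stated. With two-sided alpha 0.01, power 0.95 and odds ratio 3.3, the Hsieh formula for a binary predictor, with 30% as the event rate in unexposed patients, gives about 208 for a predictor present in half the patients and 316 for one present in 20%. A continuous predictor, with the odds ratio per standard deviation, needs 60. Other unstated predictor prevalences also reach 311. Each version is a sample size for detecting an association; none fixes the precision of a true-positive rate.

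**Step 2. Expected counts.** 300 × 0.30 = 90 necessary visits, leaving 210 unnecessary.

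**Step 3. A significant odds ratio with most necessary visits missed.** For a single binary predictor, logistic regression reduces to the 2×2 table: OR = (TP × TN)/(FN × FP), and SE(ln OR) = √(1/TP + 1/FN + 1/FP + 1/TN).

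Take TP 33, FN 57, FP 52, TN 158 (sensitivity 37%, specificity 75%):
- OR = (33 × 158)/(57 × 52) = 5214/2964 = 1.76
- SE = √(1/33 + 1/57 + 1/52 + 1/158) = 0.271
- z = ln(1.759)/0.271 = 0.565/0.271 = 2.08, P = 0.037
- Missed: 57 of 90

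With TP 32 and the same false positives, P = 0.058, so 33 is the smallest count that passes at that specificity.

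| Sensitivity / specificity | TP, FP | OR | P | Missed of 90 |
|---|---|---|---|---|
| 30% / 85% | 27, 32 | 2.38 | 0.004 | 63 |
| 30% / 80% | 27, 42 | 1.71 | 0.061 | 63 |
| 40% / 80% | 36, 42 | 2.67 | 0.0004 | 54 |

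The second row shows that not every poor tool passes. In simulation, the chance of P<.05 is 84% at 30%/85% and about 73% at 40%/75%. With 311 patients instead of 300 the results are nearly the same.

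**Step 4. What an odds ratio of 3.3 implies.** Let f be the share of patients flagged, p0 the event rate in unflagged patients and p1 the rate in flagged patients. Solve (1 − f)p0 + f·p1 = 0.30 with p1 = 3.3p0/(1 + 2.3p0). Then sensitivity = f·p1/0.30 and negative predictive value = 1 − p0.

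| f | p0 | p1 | Sensitivity | Negative predictive value |
|---|---|---|---|---|
| 10% | 0.272 | 0.552 | 18% | 73% |
| 20% | 0.246 | 0.518 | 35% | 75% |
| 50% | 0.180 | 0.420 | 70% | 82% |

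With no tool, 70% of visits are unnecessary, so that is the baseline for negative predictive value. One odds ratio is therefore compatible with missing about 73 of 90 necessary visits or 27 of 90.

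**Step 5. The opposite failure.** A LUCY that flags all 300 patients has 90/90 true positives and specificity 0. A true-positive count with nothing beside it cannot detect this.

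**The case against.** A reader might infer that the article sets up two competing verdicts on LUCY and makes P<.05 the rule for calling it effective. The text does not support that. Section 2.7.2 mentions neither LUCY nor stage 2. Its parameters and composite parameters can be read as candidate predictors, which fits the purpose given for the sample size, and the neural net is described separately in 2.6. The P<.05 sentence is a general convention that also covers the chi-squared, t and Mann–Whitney tests. Section 2.5 names one stage-2 outcome, and 2.3 already provides a blinded comparator. All of this stands.

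Two further points stand. A missing threshold, denominator or interval for the true-positive result may be left to a fuller plan that is not shown, so it is not counted here. And 3.3 is a planning value for input data taken from an earlier study, not an expected odds ratio for LUCY's combined output, so the sensitivities in Step 4 show what an odds ratio leaves open and do not forecast LUCY's performance. Whether most visits are missed depends on the flag rate.

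What the objection does not remove is the mismatch between things that are written down. The article commits to an analysis of effectiveness and to a basis for sizing stage 2, and neither measures the outcome in 2.5. The same notion of effectiveness is the stated aim of stage 2 in 2.1, and no other analysis of it is given. A detailed plan faithful to this text would inherit the problem.

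**Conclusion.** The concern holds as a mismatch: the stage-2 outcome is classification, while the stated analysis of effectiveness and the size carried into stage 2 are about association. It is worth correcting. It does not show that the investigators will declare success on P<.05.

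The size of the gap rests on 90 necessary and 210 unnecessary visits, a yes/no flag and assumed accuracy values. Under those, significance can be reached with 57 of 90 necessary visits missed, and an odds ratio of 3.3 leaves sensitivity anywhere from 18% to 70% over flag rates of 10% to 50%. Confidence is medium, because 2.7.2 can be read as covering predictors only.

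**What to change.** Amend 2.5 and 2.7.2 as follows.

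1. State that logistic regression with P<.05 evaluates candidate predictors and does not by itself establish LUCY's effectiveness.
2. State that stage 2 is assessed by LUCY's classification against the blinded cardiologist's decision for the primary endpoint.
3. Report sensitivity together with specificity and negative predictive value, each with a 95% confidence interval. Sensitivity must not stand alone, because flagging everyone satisfies it.
4. Have the investigators fix the minimum acceptable sensitivity before stage 2 starts.

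**Cost.** The wording changes, and no new kind of data is needed, since LUCY's result and the cardiologist's decision are already collected for every patient. The bar becomes harder to clear than an odds ratio above 1. Precision is limited: with 90 necessary visits and sensitivity 80%, the half-width is 1.96 × √(0.8 × 0.2/90) = 0.083, about ±8 points. The investigators should check that this is narrow enough for the minimum they choose; if it is not, wording alone will not suffice.

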## Discussion

3

The currently available data suggest that remote monitoring in addition to standard ambulatory visit improves prognosis of patient's with CIED.^[3,5]^ However, huge amount of data generated by remote monitoring system and lack of contact with patient in the era of patient-oriented medicine strongly limits a common use of remote monitoring.

Promising applications of data mining and machine learning techniques in health-measurement algorithms allow us to assume probable benefits from using modern methods of data analysis in assessment of the required ambulatory follow-up based on data gathered through remote monitoring.

## Conclusion

4

Our study is the first attempt of implementation of the machine learning and elements artificial intelligence in health care optimization of patients with CIED. LUCY will be an open product, available for additional testing and improvement with supplementary functionalities: quality of life assessment, teleconsultation, video-streaming, automated imagine recognizing.
